# RECITAL: a non-inferiority randomised control trial evaluating a virtual fracture clinic compared with in-person care for people with simple fractures (study protocol)

**DOI:** 10.1136/bmjopen-2023-080800

**Published:** 2024-02-05

**Keywords:** telemedicine, orthopaedic & trauma surgery, randomized controlled trial, protocols & guidelines, patient reported outcome measures

## Abstract

**Introduction:**

Most simple undisplaced fractures can be managed without surgery by immobilising the limb with a splint, prescribing medication for pain, and providing advice and early rehabilitation. Recent systematic reviews based on retrospective observational studies have reported that virtual fracture clinics can deliver follow-up care that is safe and cost-effective. However, no randomised controlled trial has investigated if a virtual fracture clinic can provide non-inferior physical function outcomes compared with an in-person clinic for patients with simple fractures.

**Methods and analysis:**

312 participants will be recruited from 2 metropolitan hospitals located in Sydney, Australia. Adult patients will be eligible if they have an acute simple fracture that can be managed with a removable splint and is deemed appropriate for follow-up at either the virtual or in-person fracture clinic by an orthopaedic doctor. Patients will not be eligible if they have a complex fracture that requires a cast or surgery. Eligible participants will be randomised to receive their follow-up care either at the virtual or the in-person fracture clinic. Participants at the virtual fracture clinic will be reviewed within 5 days of receiving a referral through video calls with a physiotherapist. Participants at the in-person fracture clinic will be reviewed by an orthopaedic doctor within 7–10 days of receiving a referral. The primary outcome will be the patient’s function measured using the Patient-Specific Functional Scale at 12 weeks. Secondary outcomes will include health-related quality of life, patient-reported experiences, pain, health cost, healthcare utilisation, medication use, adverse events, emergency department representations and surgery.

**Ethics and dissemination:**

The study has been approved by the Sydney Local Health District Ethics Review Committee (RPAH Zone) (X23-0200 and 2023/ETH01038). The trial results will be submitted for publication in a reputable international journal and will be presented at professional conferences.

**Trial registration number:**

ACTRN12623000934640.

STRENGTHS AND LIMITATIONS OF THIS STUDYPragmatic clinical trial embedded within two existing fracture clinics at two urban hospitals.Measures hospital-level outcomes as well as patient outcomes and experiences.Blinding of therapist or participants is not possible, although participants are blinded to the study hypothesis.Methods and results from this trial may inform the evaluation of other virtual musculoskeletal services.Study may not be sufficiently powered to determine subgroup effects, for example, based on specific fracture diagnosis.

## Introduction

In 2019, there were 178 million new fractures reported globally, an increase of 33.4% since 1990.^1^ In Australia, the treatment costs of osteoporosis-related fractures were estimated to be $A2.34 billion in 2017.^2^ With increasing numbers of people requiring care for their fractures, the burden on outpatient fracture clinics has also increased, causing long clinic wait times and productivity losses.^3 4^ The recent pandemic further strengthens the requirement for health system efficiency.

Most simple fractures, including minimally displaced fractures, can be managed conservatively without surgery. These stable fractures are managed with short-term immobilisation, advice, pain relieving medication and early rehabilitation.^5^ Traditional physical assessments at an outpatient clinic may not be required for conditions that have a clear prognosis and have been shown to recover well with conservative management.^6^

Published studies have shown that virtual fracture clinics (VFCs) can manage patients with simple fractures.^7^ Patients receive advice and management through phone calls and written handouts, rather than attending the outpatient clinic in person. Retrospective observational studies have reported that VFCs are associated with good patient satisfaction, increased cost efficiency for the hospital system, fewer adverse events and reduced presentations to in-person clinics.^8^

Despite a rise in VFCs since the recent pandemic, robust evaluations of their safety, effectiveness and cost-effectiveness are lacking. A recent systematic review of 21 publications suggested that VFCs could provide safe and cost-effective care to patients with acute fractures, though none of the included studies were randomised controlled trials.^8^ It is currently unknown whether VFCs produce non-inferior outcomes compared with in-person care for patients with simple fractures.

We have designed a clinical trial to evaluate the effectiveness of a VFC for patients with simple fractures. The primary outcome of this trial is physical function at 12-week follow-up, measured using the Patient-Specific Functional Scale (PSFS). Secondary outcomes will include health-related quality of life, patient-reported experiences, pain, health cost, healthcare utilisation, medication use, adverse events, emergency department (ED) representations and surgery. A qualitative substudy will be conducted to explore the experiences, feelings and expectations of patients who use the VFC.

## Methods and analysis

### Design

The Fracture Clinic Trial (RECITAL) is a prospective two-arm, parallel group randomised controlled trial, using a non-inferiority design with nested economic and process evaluations. We chose a non-inferiority randomised controlled trial design as both study groups are existing hospital services, and the VFC is expected to have outcomes that are at least no worse than the in-person fracture clinic. This trial has been prospectively registered with the Australian New Zealand Clinical Trials Registry (ACTRN12623000934640). This document describes the trial protocol according to the Standard Protocol Items: Recommendations for Interventional Trials 2013 Statement.^9^ Recruitment began in November 2023, with the final data collection expected to occur in November 2025.

### Setting

RECITAL will compare two existing models of care provided at two metropolitan public hospitals within Sydney Local Health District (SLHD) in New South Wales (NSW), Australia. The VFC (intervention group) is located at Royal Prince Alfred (RPA) Virtual Hospital (**rpa**virtual), while the in-person fracture clinic (control group) is situated at the RPA Hospital. **rpa**virtual is Australia’s first virtual hospital established in February 2020 to enable patients to receive hospital-level care at home through virtual means (eg, video calls or remote monitoring), rather than visiting the traditional hospital for their healthcare needs.^10^

### Eligibility criteria

Patients referred to the VFC (eg, from local emergency departments, general practices or the in-person fracture clinic) will be identified and screened by a VFC physiotherapist and an orthopaedic doctor to determine if the patient is suitable for either model of care (virtual or in-person). The RECITAL study staff will contact eligible patients to invite them into this study. Figure 1 illustrates the trial design.

**Figure 1 F1:**
[figure not shown]
Trial design. AE, adverse events; ED, emergency department; EQ-5D-5L, EuroQol 5 Dimensions 5 Levels; GS-PEQ, Generic Short Patient Experiences Questionnaire; NRS, Numerical Rating Scale; PSFS, Patient-Specific Functional Scale; SAE, serious adverse event.

Patients will be invited to participate if they meet the following criteria:

Have an acute (<6 weeks old) simple fracture that can be managed using a removable orthoses (eg, shoulder immobiliser, CAMboot or wrist splint).Aged ≥18 years.Have a condition that is deemed appropriate for virtual management by an orthopaedic doctor.Has access to a phone and will be within New South Wales at the time of consult.Is willing to participate and comply with the study requirements.Have a radiology scan or report to confirm the nature of the injury.

Patients will be excluded if they have:

Complex or significantly displaced fracture, including pathological, open, unstable or spinal fractures requiring a cast or surgical management.Neurovascular concerns.A condition not managed by RPA Hospital Orthopaedics Department.Reported being unable to attend the in-person fracture clinic within the recommended follow-up time.Opted out.

People with any type of simple fracture that is deemed appropriate for virtual care will be eligible for the trial, to reflect usual practice. The most common types of fracture are expected to be base of fifth metatarsal, ankle Weber A, and Mason I radial head. Uncommon types of simple fracture could include greater tuberosity or clavicle. Patients who consent to participate and complete their baseline measures will be enrolled in this study. Informed consent (online supplemental file 1) and study data will be collected and managed using the Research Electronic Data Capture (REDCap) tool hosted at SLHD.^11 12^ The randomisation schedule will be computer-generated using REDCap’s randomisation model and will be stratified in random blocks of 4, 6, 8 and 10 to ensure equal numbers in both groups and concealed allocation. A biostatistician not involved in this study will set up the allocation schedule and upload it into REDCap. Only the biostatistician will be aware of the allocation to ensure concealment. The study coordinator will randomise the patients to the study groups. Participants randomised to the VFC who agree to participate in the qualitative substudy will be purposively selected for an interview according to their age, employment status, tertiary education level, type of injury and discharge status. Selected participants will be contacted once they are discharged from the clinic to ensure their complete experience with the VFC is captured.

10.1136/bmjopen-2023-080800.supp1Supplementary data

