### VFC (intervention group)

Patients randomised to the VFC (intervention) group will be contacted via phone and email to organise an initial follow-up with a physiotherapist; usually within 5 days after their referral is received. Patients are sent an email with their appointment details and a fracture management fact sheet. The fact sheet explains their clinical condition, expected recovery, early rehabilitation exercises, activity limitations and information on care escalation. These fact sheets were adapted with permission from Royal Melbourne Hospital’s VFC.

All patients are offered a video consultation with a physiotherapist unless they choose to have their review via phone. During the virtual consults, the physiotherapist conducts an assessment, discusses the X-ray findings and provides a management plan. The virtual consult sessions are usually approximately 30 min. An email summary of the consultation and follow-up appointment details are sent to the patient after the consultation. A Physitrack link may also be included in this email. Physitrack or PhysiApp is an internet-based programme that allows patients to view videos of their prescribed exercises. Patients are usually offered a follow-up virtual appointment at 2 weeks and 6 weeks post-fracture, or based on clinical need. Patients can contact the physiotherapist out of session if they have any concerns during their care period. Most patients are discharged from the VFC at 6 weeks post-fracture if there are no concerns. Patients will be supported with an interpreter, Aboriginal Cultural Support Team or with loaned devices and data as required. For example, although many older patients (aged 60+) currently use the virtual service, a digital patient navigator can assist patients and provide a smart phone with data so they can attend their virtual clinic appointments. We will monitor patient adherence by the number of consults attended; and the number of ad hoc patient contacts via phone or email with the clinic.

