### In-person fracture clinic (control group)

Patients randomised to the in-person fracture clinic will be contacted via phone or email to provide a follow-up appointment. Appointments usually occur 7–10 days after the referral is received, based on the availability of the on-call orthopaedic doctor. Clinical management and subsequent follow-ups of the control group will be determined by the orthopaedic doctors at the in-person fracture clinic. Clinical management can include a physical assessment by a doctor, radiology scan, advice and exercises. A physiotherapist may be involved in the patient’s care. Patients in the control group may receive written instructions about their recovery and exercises as per current processes. The in-person consult sessions are usually approximately 20 min. Current practice suggests that patients may attend the in-person fracture clinic once or twice within 6 weeks post-fracture. We will monitor patient adherence by the number of consults attended.

Staff providing care to study participants will be trained on the trial protocol and be regularly supported by study investigators to ensure adherence to study protocol.

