### Primary analysis

Non-inferiority trials assess whether an intervention outcome is not clinically worse than a control. The PSFS score at 12 weeks post-randomisation is the primary outcome in this study and we have prospectively defined a non-inferiority margin (ΔT) of −0.7 points, which is the maximum difference we are prepared to tolerate and still consider virtual care not to be clinically inferior to in-person care. The null hypothesis is, therefore, that a difference of greater than ΔT exists in favour of in-person care (H0: Δ ≤−ΔT). This will be assessed by creating a 95% CI, which should be entirely above the non-inferiority margin for the intervention to be declared non-inferior. The PSFS score will be compared between treatment groups as the dependent variable in a generalised linear regression model for the primary analysis adjusting for baseline PSFS variables. The treatment difference will be based on the estimate of adjusted means and 95% CIs.

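### Entry is open until 6 weeks after fracture and care is timed from fracture, but the primary PSFS is timed from randomisation and the primary model has no term for time since fracture

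*Protocol article*

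**What the plan says.** The Eligibility criteria admit adults who "Have an acute (<6 weeks old) simple fracture that can be managed using a removable orthoses". The same section lists referral sources as, for example, "local emergency departments, general practices or the in-person fracture clinic". No exclusion criterion removes a patient who has already been reviewed at the in-person clinic.

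Care follows a clock that starts at fracture. In the virtual arm, the first review is "usually within 5 days after their referral is received". After that, "Patients are usually offered a follow-up virtual appointment at 2 weeks and 6 weeks post-fracture, or based on clinical need", and "Most patients are discharged from the VFC at 6 weeks post-fracture if there are no concerns". In the control arm, the first appointment is usually 7–10 "days after the referral is received, based on the availability of the on-call orthopaedic doctor", and "patients may attend the in-person fracture clinic once or twice within 6 weeks post-fracture".

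The outcome follows a different clock. Under Primary analysis, "The PSFS score at 12 weeks post-randomisation is the primary outcome". The Abstract, Introduction and Outcomes sections give 12 weeks without an anchor. The primary model is a generalised linear regression whose only named adjustment is baseline PSFS. The protocol gives no expected distribution of fracture age at entry and names no stratification by it.

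**The concern.** The randomised contrast is largely a contrast in how follow-up is delivered during the first 6 weeks after fracture. A participant who enters near the end of that period has little of it left, so allocation may change less of their care. A participant referred on from the in-person clinic may have had some comparator care before randomisation. In either case the two arms may look more alike for that participant. In a superiority trial this would cost power. In a non-inferiority trial analysed by intention to treat, it moves the average difference towards zero and so towards the conclusion hoped for.

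There is also a smaller matter of efficiency. Participants measured at the same nominal time point can be up to 6 weeks apart in recovery. Fracture age at randomisation is a baseline value that plausibly predicts function, and it must be known to check eligibility, but the stated model does not use it.

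**Working it through.** **Inputs from the protocol.** Margin 0.7, SD 2.0, baseline–final correlation 0.5, N = 312, 10% loss, 90% power (Sample size). Non-inferiority requires the 95% CI to lie entirely above -0.7 (Primary analysis), which is a one-sided 2.5% test.

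**The plan's own figure.** Per arm, n = 2 × 2.0² × (1.645 + 1.282)² / 0.7² = 139.8, so 140 per arm and 280 in total; 280 / 0.9 = 311.1, so 312. The stated N reproduces at one-sided 5% with SD 2.0. Nothing below changes it; it supplies the 140 evaluable per arm.

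**Timing.** I take fracture age at entry as fracture age at randomisation.
- Earliest possible endpoint: about 0 + 12 = 12 weeks after fracture.
- Latest possible endpoint: just under 6 + 12 = 18 weeks after fracture.
- For entry on day 41, with the referral received that day (assumption), a virtual review within 5 days comes by day 46 and a control visit at 7–10 days comes on days 48–51. The 6-week mark is day 42. The virtual review would therefore fall at about the usual discharge point, and the control visit after the period in which control attendance is described.

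**Illustration of dilution.** The documents give neither the share f of late or previously reviewed entrants nor the contrast they retain, so both are assumptions. Set the true difference in all other participants at -0.7.
- Adjusted SD = 2.0 × √(1 − 0.5²) = 1.732.
- SE = 1.732 × √(2/140) = 0.2070.
- With no contrast in the share f, the average difference is -0.7(1 − f), and P(declare non-inferiority) = Φ(0.7f / 0.2070 − 1.96).
- If that share keeps half the contrast, replace f by f/2.

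| f | Average difference (no contrast) | P, no contrast | P, half contrast kept |
|---|---|---|---|
| 0 | -0.700 | 2.5% | 2.5% |
| 5% | -0.665 | 3.7% | – |
| 10% | -0.630 | 5.2% | 3.7% |
| 20% | -0.560 | 10.0% | 5.2% |
| 30% | -0.490 | 17.2% | 7.3% |

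With the unadjusted SD of 2.0, the no-contrast values at 10% and 20% are 4.8% and 8.5%.

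**Value of the covariate.** If time since fracture explains a further share R² of residual variance, CI width is multiplied by √(1 − R²). This is 0.975 at 5% and 0.949 at 10% (both R² values assumed), so the CI is about 2.5% to 5% shorter. Under the 95% CI rule with 280 evaluable participants and a true difference of zero, power moves from 92.2% to 93.4% or 94.6%.

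**Cost of making a subset decisive.** At SD 1.732, a subset holding 70% of the 280 has 98 per arm: SE = 1.732 × √(2/98) = 0.247, and power = Φ(0.7/0.247 − 1.96), about 81%. At 50% there are 70 per arm, SE = 0.293, and power is about 67%.

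**The case against.** The strongest reply is that none of this is an error. The trial compares two existing services in the patients those services receive, and the protocol says that any suitable simple fracture is eligible so as to reflect usual practice. Timing an outcome from randomisation while clinics schedule visits from injury is ordinary in a pragmatic trial. On that view, the average over everyone referred is the target. If 10% of participants have no contrast and the rest are at -0.7, the average is -0.63, which lies inside the margin, and declaring non-inferiority is then correct. This stands. A reader might take the 5.2% and 10.0% above as inflated false-positive rates for the trial, but they are not: type I error for the all-referred population remains 2.5%.

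A reader might also infer that late entrants certainly dilute the contrast because their recovery is largely over. The protocol does not support that. Discharge at 6 weeks applies to most patients and only where there are no concerns, and virtual visits may also follow clinical need, so a late entrant may still receive care that differs by arm. The described schedules suggest that early entry is usual, and with a late share below about 5% the illustrated figure is 3.7% or less. The in-person clinic is one example among the referral sources, with no frequency given, and the text does not say that patients sent from there have already been reviewed.

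Finally, leaving time since fracture out of the model does not bias a randomised comparison. Allocation balances it in expectation, and baseline PSFS may capture part of it. Further covariates may also be set out in an analysis plan that is not available here.

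What the reply does not remove is that the protocol itself fixes the eligibility window, both clocks and the named adjustment. As they stand, a reader of the result could not tell whether non-inferiority rests on participants whom allocation could still affect.

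**Conclusion.** The point holds as a design mismatch with a cheap remedy; it does not show a biased primary analysis. The primary PSFS falls about 12 to 18 weeks after fracture, care in both arms is described over the first 6 weeks, and some participants may come from the comparator clinic. Reduced contrast in late or previously reviewed entrants is possible and would act in the direction of non-inferiority, but its size cannot be derived from the protocol. The rise from 2.5% to 3.7%, 5.2% or 10.0% at late shares of 5%, 10% or 20% depends on three assumptions: early entrants are the population of interest, their true difference is exactly -0.7, and late entrants have no contrast at all. The covariate gain is a CI about 2.5% to 5% shorter, if it explains 5% to 10% of residual variance. It is a gain in precision only and does not undo dilution. A reader might conclude that non-inferiority should be claimed only if an early-entry subset agrees. That goes too far: it would make an underpowered subset decisive, and the protocol offers no basis for any particular cut-off.

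**What to change.** 1. State how the eligibility window, the two care schedules and the randomisation-based endpoint fit together, and give the 12-week anchor wherever the endpoint is named.
2. Add days from fracture to randomisation as a pre-specified covariate in the primary model, alongside baseline PSFS.
3. Record whether each participant had an in-person fracture clinic review before randomisation.
4. Report the distribution of fracture age at randomisation by arm.
5. Pre-specify a supportive analysis against the same -0.7 margin by time since fracture and by prior in-person review. It should not gate the primary conclusion and needs no fixed early-entry cut-off.

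The cost is one model term, one extra data item and one supportive analysis whose CI will be wider than the primary one. Sample size, eligibility and clinical care stay as they are.

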### Outcomes

The primary outcome of this study will be the participant’s physical function assessed using the PSFS at 12 weeks. This self-reported tool has shown to be sensitive to change in patients with musculoskeletal problems, including simple fractures.^13–15^ Participants list up to five functional tasks at baseline and score their level of ability — 0 (unable to perform activity) to 10 (able to perform activity at the same level as before the injury). Scores for each activity will be summed and calculated as an average of the total possible score for the participant (determined by the number of identified activities). We will compare the PSFS average scores between groups at 12 weeks as our primary measure. Table 1 summarises the outcome measures for this study.

**Table 1 T1:** Outcome measures

Milestones	Baseline	6 weeks	12 weeks
Patient characteristics	✓		
Patient-Specific Functional Scale	✓	✓	✓
EuroQol 5D-5L	✓		✓
Pain Numerical Rating Scale	✓	✓	✓
Generic Short Patient Experiences Questionnaire		✓	
Health costs			✓
Healthcare utilisation			✓
Medication use		✓	
Adverse events and serious adverse events		✓	✓
Emergency department representations			✓
Patients requiring surgery			✓

EuroQol-5D-5L, EuroQol 5 Dimensions 5 Levels.

Secondary measures for this study will include:

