### Blinding

The participants, therapists and assessors will not be blinded. The surveys administered during this trial are self-assessments completed by patients directly in REDCap who will be blinded to the study hypothesis. If required, an independent blinded assessor may contact the patient to assist them with completing their surveys.

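### The interview trigger opens a research contact in the virtual fracture clinic arm only, usually before the unblinded, self-reported 12-week primary outcome; holding it until the 12-week surveys are in is a cheap improvement

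*Protocol article*

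**What the plan says.** The relevant statements are spread over several sections of the protocol article.

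- **Who is interviewed** (end of Eligibility criteria): "Participants randomised to the VFC who agree to participate in the qualitative substudy will be purposively selected for an interview". Selection is on age, education, employment, injury type and discharge status. The Introduction describes the substudy as being about users of the VFC. No in-person counterpart appears anywhere.
- **When they are approached** (same paragraph): "Selected participants will be contacted once they are discharged from the clinic to ensure their complete experience with the VFC is captured".
- **When discharge happens** (VFC, intervention group): "Most patients are discharged from the VFC at 6 weeks post-fracture if there are no concerns".
- **When the primary outcome falls** (Primary analysis): "The PSFS score at 12 weeks post-randomisation is the primary outcome in this study".
- **How it is measured** (Outcomes; Blinding): the PSFS is self-reported, and "The participants, therapists and assessors will not be blinded". The mitigation offered is that patients complete the surveys themselves and are people "who will be blinded to the study hypothesis".

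The Generic Short Patient Experiences Questionnaire (GS-PEQ) is collected once, at 6 weeks. Pain and EQ-5D-5L are also self-reported at 12 weeks.

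**The concern.** The trial compares two existing services. A research interview belongs to neither of them, so anything it does to later answers is not an effect of virtual care. Here it is offered in one arm only, and the stated trigger tends to place it before the outcomes that decide the trial. Talking at length about the virtual service is additional attention that controls do not receive, and it could colour how an unblinded participant later rates function, pain or experience.

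In a non-inferiority comparison the direction matters. A favourable shift confined to the VFC arm would move the estimate away from the margin of −0.7 and make non-inferiority easier to declare. An unfavourable shift would do the reverse.

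**Working it through.** **Step 1: timeline.** Let *a* be the age of the fracture at randomisation, in weeks. The inclusion criterion is "Have an acute (<6 weeks old) simple fracture", so *a* lies between 0 and just under 6.

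- Usual discharge, and so the opening of contact: week 6 after fracture.
- Primary PSFS: week *a* + 12 after fracture, that is, week 12 to about week 18.
- Interval from contact to primary outcome: (*a* + 12) − 6 = *a* + 6 weeks, so at least 6 weeks. The upper end, close to 12, is nominal, because late entrants may be discharged later than usual.
- GS-PEQ: if its 6 weeks also run from randomisation (the article does not give the origin), it falls at week *a* + 6 after fracture. That is *a* weeks after usual discharge. Contact can then open on the same date or earlier.

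For the usual course, contact therefore opens before the primary outcome. Only participants discharged 6 or more weeks later than usual could fall after it.

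**Step 2: number analysed.** The planned total reproduces as follows. With SD 2.0, margin 0.7, 90% power and one-sided 5%, n = 2 × 2.0² × (1.645 + 1.282)² / 0.7² ≈ 140 per arm, or 280 in total. Then 280 / 0.9 = 311.1, which is 312 when rounded up to equal arms. The expected number analysed per arm is 312 × 0.9 / 2 = 140.4. Nothing else in this point depends on the sample size.

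**Step 3: illustration of size.** The number interviewed (*k*) and the mean PSFS shift among them (*s*) are assumptions; the documents give neither.

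- Shift in the VFC mean: *b* = *k* × *s* / 140.4.
- Baseline-adjusted SD: 2.0 × √(1 − 0.5²) = 1.73. Standard error of the difference: 1.73 × √(2 / 140.4) = 0.207.
- Chance of declaring non-inferiority when the true difference is exactly −0.7: 1 − Φ(1.96 − *b* / 0.207), which is 2.5% when *b* = 0 (two-sided 95% CI).

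| *k* | *s* | *b* | *b* / 0.7 | False non-inferiority at the margin |
|---|---|---|---|---|
| any | 0 | 0 | 0% | 2.5% |
| 15 | 0.1 | 0.01 | 1.5% | 2.8% |
| 30 | 0.2 | 0.04 | 6% | 4.0% |
| 10 | 0.5 | 0.04 | 5% | 3.7% |
| 20 | 0.5 | 0.07 | 10% | 5.3% |
| 20 | 1.0 | 0.14 | 20% | 10.2% |
| 40 | 1.0 | 0.28 | 41% | 28.0% |

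A negative *s* moves the estimate towards the margin and lowers the last column. The lower rows need a large effect: 0.5 to 1.0 points is 38% to 77% of the 1.3-point small-change value quoted under Sample size (0.5 / 1.3 and 1.0 / 1.3). It would have to arise from one conversation and last for weeks.

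**The case against.** The strongest reply is that the article dates the approach and not the interview. Discharge is an earliest point, no interview window is given, and a condensed article may leave scheduling, numbers and interviewer to the full protocol. This stands as a limit. A reader might infer that all interviews take place before week 12, or that the research team conducts them. The text says neither; it gives the team a role only in working on the transcripts. What remains is the trigger, which the article does state and which usually opens contact ahead of the outcome.

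A reader might also infer a demonstrated bias towards non-inferiority. The documents do not support that. An interview could bring out dissatisfaction as readily as goodwill, and selecting on discharge status may deliberately include people with less straightforward courses. The PSFS rates named tasks against pre-injury ability, so a lasting effect of one conversation is not obvious.

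Two further mechanisms are weak:

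- **Loss of blinding to the hypothesis.** Participants already know their arm, and the recruitment script (Consent or assent) tells everyone about both follow-up options. Being asked about one's own clinic does not reveal a non-inferiority hypothesis. At most it hints that the virtual service is the one of interest.
- **Better retention in the VFC arm.** The reminders, the phone call and the A$50 for completing all surveys apply to both arms.

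Finally, the timing has a stated purpose, to capture the whole VFC experience, and waiting costs recall. That is a genuine trade-off. The purpose itself, however, requires only that contact follow discharge, and a later approach still meets it.

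**Conclusion.** The point holds as an avoidable weakness of design. It is neither a contradiction in the protocol nor a shown bias. As written, the trigger usually opens a one-arm research contact at least 6 weeks before an unblinded, self-reported primary outcome, and possibly before the GS-PEQ.

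Its effect cannot be sized from the documents. Because only a selected subset is interviewed, it is probably small. The tabulated values of *b* rest wholly on assumed interview numbers and assumed favourable shifts, and they should not be cited as an estimate. The conclusion rests on three things: the usual discharge time, the 12-week timing from randomisation, and the absence of any stated hold. If the full protocol already delays the interviews, only the wording here needs to change.

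**What to change.** Replace the trigger with wording such as: *Contact for interview will be made after discharge from the VFC and after the participant's 12-week surveys have been submitted (or the 12-week window has closed).* If this is already the practice, state it.

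The cost is somewhat longer recall: interviews would take place at roughly 12 to 18 weeks after fracture, typically 6 or more weeks after discharge. No visits, staff or sample size are added. The change needs the approvals named under Ethics and dissemination (steering committee and ethics committee).

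Recruitment began in November 2023, so some interviews may already have been held. Record their dates, and report how many preceded the 6-week and 12-week surveys. Do not repeat the primary comparison with interviewees removed from the VFC arm. They are purposively selected, partly on discharge status, which arises after randomisation and may be related to function. Removing them from one arm only would break the randomised comparison, and any change in the result could reflect selection instead of the interview.
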